### Statistical analysis

2.7

The statistical analysis of study data is conducted by the Tiresia Coordination Center at the Istituto di Ricerche Farmacologiche Mario Negri IRCCS. Analyses will employ various analytical techniques to address the study objectives and research questions. Descriptive statistics, including proportions, medians and interquartile ranges, and means and standard deviations, will be used to summarize and present the collected data.

The primary analysis focuses on identifying prognostic factors predictive of the identified outcome measures and in particular: the achievement of the three objectives in the rehabilitation process (i.e., successful decannulation, trunk control and complete oral feeding); a pathological result in the five cognitive domains investigated by the OCS (attention, language, numerical cognition, praxis and memory) (20); the value of the GOS-E scale, simplified into 4 levels (death or vegetative state, severe disability, moderate disability, good recovery); the value of the SRS scale, simplified into five levels (independent, night supervision, part-time supervision, indirect full-time supervision, direct full-time supervision). Separate regression models will be developed for each outcome and timing (4 and 12 months from the acute event). Logistic regression models will be used to assess the achievement of the rehabilitation objectives and the abnormalities in the OCS cognitive domains, which are dichotomous variables. Multinomial logistic regression models will be used to handle the GOS-E and SRS scales, which are categorical variables with four and five levels, respectively. To account for the large number of candidate predictors to screen as potential prognostic factors, we will use the technique of Least Absolute Shrinkage and Selection Operator (LASSO) (21), which is a popular approach to perform variable selection when the number of potential predictors is large compared with the sample size (22).

The secondary analysis of the study is aimed at developing quality of care indicators for sABI Units. This step will leverage the prognostic models developed for the main analysis, which will be employed to calculate the expected number of failures for each dichotomous outcome and the expected value of each of the possible levels for the categorical variables. Because the models will be developed using all patients admitted to all participating centers, they represent the average behavior and can be used as a reference (or benchmark) for quality-of-care assessment. The comparison in each sABI Unit between the expected and observed frequencies of the outcomes will constitute the indicator of quality of care for the department. The most common approach to perform this comparison is the standardized event ratio (SER), i.e., the ratio of observed and expected events (23). A SER value less than 1 indicates a lower-than-average number of events, while a value greater than 1 indicates that a center experienced more events than expected. Each SER will be provided with the corresponding confidence interval. Importantly, SER heavily relies on the prognostic model used as a benchmark of quality of care. In order to assess the robustness of the results against the prognostic model developed, indicators based on nonparametric methods, independent of that model, will also be used. In particular, a matching-based design will be applied (24). For each center, each patient will be matched to *K* other patients admitted to different units but similar to the selected patient with respect to the identified prognostic factors. Matching will be performed using state-of-the-art algorithms, including optimal and cardinality matching. This strategy will create a control group for each center with a similar case mix with respect to the relevant prognostic factors. The quality of care will be measured in terms of risk difference for each failure indicator, provided with the appropriate confidence interval. The parameter *K*, which sets how many control subjects will be matched to each patient, will be chosen based on the size of the database. We expect to be able to perform this analysis with a value of *K* between 1 and 3.

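### For the middle levels of GOS-E and SRS, an observed-to-expected ratio has no fixed direction, so it cannot serve as a quality-of-care indicator

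*Protocol article*

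**What the plan says.** The protocol article, section 2.7 (Statistical analysis), reduces GOS-E to a scale "simplified into 4 levels (death or vegetative state, severe disability, moderate disability, good recovery" and SRS to one "simplified into five levels (independent, night supervision, part-time supervision, indirect full-time supervision, direct full-time supervision". Each list runs in one direction, from worst to best for GOS-E and from least to most supervision for SRS. The model is unordered: "Multinomial logistic regression models will be used to handle the GOS-E and SRS scales, which are categorical variables with four and five levels, respectively".

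For the quality indicators, the same section uses the models to obtain the expected number of failures for each binary outcome and "the expected value of each of the possible levels for the categorical variables". It continues: "The comparison in each sABI Unit between the expected and observed frequencies of the outcomes will constitute the indicator of quality of care for the" unit. The SER is named as the most common way to make the comparison, and it is read as a count: "A SER value less than 1 indicates a lower-than-average number of events, while a value greater than 1 indicates that a center experienced more events". The matching analysis has its own measure: "The quality of care will be measured in terms of risk difference for each failure indicator".

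The article gives no favourable direction, cumulative cut-point or single ordinal summary for GOS-E or SRS. It also does not say what counts as a failure on either scale.

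**The concern.** For a binary failure, more events than expected means worse results. The extreme levels of an ordered scale work the same way: an excess of death or vegetative state is bad, and an excess of good recovery is good. A middle level is different, because patients can leave it by improving or by deteriorating, and can enter it from either side. A ratio above or below 1 there says only that the unit has more or fewer patients in that category. It does not say whether they are better or worse off.

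The Conclusion of the article envisages audits in centres whose quality of care deviates significantly from the average. A significant ratio on a middle level could mark a unit as deviating when its direction is unknown. A unit with a real shift could also sit at 1.

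The matching analysis has a related gap. It needs a failure event, and none is stated for these two scales.

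**Working it through.** **The plan's own figures.** Section 2.8 assumes 15 centres, 60 patients per unit per year and 30 months: 15 × 60 × 2.5 = 2,250 patients, or 150 per unit. Its predictor count is 0.10 × 2,250 / 10 = 22.5, given as 22, so it reproduces. It concerns binary logistic models and contains nothing on the indicators for GOS-E or SRS.

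**How many indicators are affected.** GOS-E has 4 levels, 2 of them in the middle. SRS has 5 levels, 3 in the middle. Per time point that is 9 level-wise comparisons, of which 5 are middle levels.

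**General argument.** Relative to the benchmark, an improving unit changes the count in a middle level by (inflow from worse levels) − (outflow to better levels). Both terms are zero or positive, so the net sign is undetermined. The worst level has outflow only and the best has inflow only, so their signs are fixed.

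**Numerical check.** The documents give no level distributions and no effect size. I assume three benchmark distributions and a unit whose cumulative odds are multiplied by 1.5 or by 1/1.5. For each cumulative benchmark proportion *c*, the shifted value is *c′* = *o*/(1 + *o*), with *o* = OR × *c*/(1 − *c*). Level probabilities are differences of successive *c′*, and O/E is the shifted probability divided by the benchmark one.

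*GOS-E 10/20/30/40% (worst to best), cumulative 0.10, 0.30, 0.60.*
- Worse unit: 0.1429, 0.3913, 0.6923. Moderate disability: (0.6923 − 0.3913)/0.30 = 1.00.
- Better unit: 0.0690, 0.2222, 0.5000. Moderate disability: (0.5000 − 0.2222)/0.30 = 0.93.

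*GOS-E 10/40/30/20%, cumulative 0.10, 0.50, 0.80.*
- Worse unit: 0.1429, 0.6000, 0.8571. Moderate disability: (0.8571 − 0.6000)/0.30 = 0.86.
- Better unit: 0.0690, 0.4000, 0.7273. Moderate disability: (0.7273 − 0.4000)/0.30 = 1.09.

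*SRS, five levels of 20% (independent first), cumulative 0.20, 0.40, 0.60, 0.80.*
- Better unit: 0.2727, 0.5000, 0.6923, 0.8571. Part-time supervision: (0.6923 − 0.5000)/0.20 = 0.96.
- Worse unit: 0.1429, 0.3077, 0.5000, 0.7273. Part-time supervision: (0.5000 − 0.3077)/0.20 = 0.96.

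The same shifted distributions give these ratios for cumulative events:

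| Assumed benchmark | Middle level: worse / better unit | Cumulative event | Cumulative O/E: worse / better unit |
|---|---|---|---|
| GOS-E 10/20/30/40% | 1.00 / 0.93 | severe disability or worse | 0.3913/0.30 = 1.30 / 0.2222/0.30 = 0.74 |
| GOS-E 10/40/30/20% | 0.86 / 1.09 | severe disability or worse | 0.60/0.50 = 1.20 / 0.40/0.50 = 0.80 |
| SRS 20% each | 0.96 / 0.96 | full-time supervision or more | 0.50/0.40 = 1.25 / 0.3077/0.40 = 0.77 |

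**An example without a common odds ratio.** Take a GOS-E benchmark of 25% per level and two units at 15/20/25/40% and 40/20/25/15%. Their level ratios are 0.6/0.8/1.0/1.6 and 1.6/0.8/1.0/0.6. The middle ratios are identical although the units are opposite. For severe disability or worse, the ratios are 35/50 = 0.70 and 60/50 = 1.20. With levels scored 1 to 4, the mean levels are 2.90 and 2.15 against 2.50, so observed minus expected is +0.40 and −0.35.

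**The case against.** **The levels can be read together.** This stands in part. In the last example the extreme levels separate the two units (0.6 and 1.6 against 1.6 and 0.6). A reader might infer that the whole GOS-E or SRS assessment is uninterpretable; it is not. Only the middle-level ratios lack a direction, and nothing in the article says that they are to be read only alongside the extremes.

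**The article does not literally promise an SER for each level.** Correct. It gives expected values per level, makes observed versus expected frequencies the indicator, and names the SER as the common approach. A ratio per level is the natural reading. Details may sit in an analysis plan that is not shown, but the level-by-level basis is stated in the article itself.

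**The fault is not in the multinomial model.** Correct. A proportional-odds model followed by level-wise ratios would have the same problem.

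**A reader might infer that ignoring the order costs the prognostic models much power.** The documents do not support that:
- They give no effect size or power for these scales, and predictors are selected by LASSO, not by single-covariate tests.
- A predictor with 87% power on 1 df at n = 1,000 has, at the planned 2,250, about 99.6% on 1 df, 98.3% on 3 df and 97.4% on 4 df, so the loss is 1 to 2 points.
- Any gain from an ordinal model depends on roughly proportional odds. For a polarised unit of 150 patients (32/18/18/32% against 25% each, compared with 2,100 others), simulated power was 81% for the unordered test and 7% for the ordinal one.

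The multinomial model is valid and makes no proportionality assumption. Keeping it is defensible.

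**Conclusion.** The concern holds for the indicators and not for the choice of regression model. Per time point, 5 of the 9 level-wise comparisons have no fixed direction. In the examples, a middle-level ratio is the same in a better and a worse unit (0.96 and 0.96), or reverses its reading with case mix (better against worse: 0.93 and 1.00, then 1.09 and 0.86).

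The absence of direction follows from the structure of an ordered scale and needs no assumption about proportional odds. The particular figures do rest on assumed level distributions and an assumed odds ratio of 1.5.

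The reach is limited. Section 2.2 makes GOS-E and SRS secondary outcomes. The three primary binary outcomes and the binary OCS domains are unaffected, and so are the extreme levels of both scales. The change is still worth making before analysis, because it is nearly free and also supplies the failure event that the matching analysis lacks for these scales.

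**What to change.** 1. Keep the multinomial models if preferred. For each patient, sum the predicted probabilities into cumulative events, for example severe disability or worse for GOS-E and full-time supervision (indirect or direct) or more for SRS. Report each unit's O/E with a confidence interval on those events. Observed minus expected mean level is an alternative, if the scoring is fixed in advance.
2. Use the same cumulative events as the failure indicators in the matching analysis, so that the SER and the risk difference address the same outcome.
3. State for each indicator which direction is favourable. Level-wise frequencies can still be shown descriptively.
4. Name the main cut-points before analysis and show the other thresholds beside them (3 in all for GOS-E, 4 for SRS). One cut-point can miss a polarised unit: at 32/18/18/32% against 25% each, severe disability or worse gives 50/50 = 1.00, while death or vegetative state gives 32/25 = 1.28.
5. Optionally add a proportional-odds or partial proportional-odds model as a sensitivity analysis. It may be more efficient for weak predictors if proportionality holds.

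The cost is a few sentences of analysis wording, slightly more code and an advance choice of cut-points. Data collection does not change.

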### Sample size calculation

2.8

Each sABI Unit admits an average of 60 patients per year. When the study was designed, we assumed that 15 centers would have actively enrolled patients. Accordingly, we expected to collect data on about 900 patients per year. To develop a logistic regression model, it is common to consider adequate a sample that has at least 10 events for each predictor included in the model (25). Extending the data collection for 30 months and assuming that failure indicators are infrequent (10% of the case series), it will be possible to develop predictive models that include 10% * 2,250/10 = 22 predictors. Thus, we will be able to investigate the independent prognostic value of several factors and, with such a large number of predictors, it will be possible to develop accurate prognostic models to be used in the planned quality-of-care indicators.

## Study monitoring

3

The Tiresia Coordination Center oversees the centralized monitoring of study data, ensuring adherence to study protocols, data quality standards, and ethical guidelines. Through regular quality reports and ongoing communication with participating centers, the Coordination Center will identify and promptly address data discrepancies, protocol deviations, and emerging issues. Sample-based site visits, including virtual meetings and on-site assessments, further enhance data monitoring and quality assurance efforts, fostering collaboration and accountability among study stakeholders.

## Ethics and dissemination

4

Ethical approval for the study has been granted by the Section of the Lombardy Region of Fondazione Don Gnocchi IRCCS Ethics Committee (study code: 03_07/04/2021). The study adheres to stringent ethical standards and regulatory guidelines to protect patient privacy and the confidentiality of the collected information throughout the research process. Informed consent procedures ensure that patients or their legal representatives are fully informed about the study objectives, procedures, and potential risks before providing consent for participation. Special provisions are made for patients unable to provide informed consent due to the severity of their clinical condition, ensuring that their rights and interests are safeguarded in accordance with ethical guidelines and regulatory requirements. In Italy, whenever the patient does not have a legally recognized representative and has never been, while in the rehabilitation unit, in the conditions to give truly informed consent, consent can be waived or delayed. In particular, at the moment when the ethical approval was granted, the Italian Data Protection Authority (DPA) provided special prescriptions for the processing of data that are necessary for the conduct of studies enrolling persons who, due to the severity of their clinical condition, are unable to understand the indications made in the information and validly give consent (26). The DPA authorized the processing of personal data of such patients, even in the absence of their informed consent, subject to the limits and conditions specified in the provision (Chapter 5 of Annex 1: “Prescrizioni relative al trattamento dei dati personali effettuato per scopi di ricerca scientifica”). Specifically, these conditions are met in the specific case of patients without a legally recognized representative who are not in the condition of giving informed consent. Relatives or persons closest to the patient will be informed of the research in any case.

All requirements about communication, dissemination and security indicated by the DPA for the processing of sensitive data will be respected. In particular, data security measures are implemented to protect sensitive patient information and comply with national and European regulations governing the use of personal data for research purposes. Patient data are pseudonymized and encrypted to prevent unauthorized access or disclosure, with access restricted to authorized personnel via secure authentication mechanisms. Data storage and transmission protocols adhere to strict security standards, minimizing the risk of data breaches or unauthorized access.

## Conclusion

5

The present study, promoted by the Tiresia network, represents a comprehensive effort to address critical gaps in sABI research and practice through a multicenter, prospective study design. Specifically, the overarching goal of the study is to assess the quality of care in sABI units using outcome indicators while accounting for differences in patient case-mix based on prognostic factors measured at admission. Notably, the study is not focused on the assessment of the effectiveness of specific treatments, interventions or policies. Determining treatments associated to the best outcomes is a medium-to-long term goal of the Tiresia network, which can be achieved by performing audits and further investigations in the centers showing a quality of care significantly deviating from the average. This study will therefore offer the possibility to generate hypotheses on the effectiveness of methods of care, which will be tested with further studies, possibly extending the data collection and leveraging the formed network of sABI units.

A distinctive and innovative feature of the study is the unprecedented number of participating centers (27 sABI units), whose involvement has been facilitated by the Tiresia network. The study aims at establishing one of the largest data collections in the field in Italy and internationally in terms of patient enrollment. Such a broad participation provides a robust platform for collecting diverse and comprehensive data, enhancing the generalizability and relevance of study findings.

Another strength of the study lies in its robust underlying methodology, which is evident in several aspects of the study design. These include the standardized definition of primary outcome measures using the ICF framework, the implementation of stringent data quality control procedures to ensure consistency in data collection across sites, and the application of advanced statistical methods to identify deviations from the average quality of care among the centers.

This research endeavor will be a unique opportunity to advance knowledge and improve outcomes for sABI patients across Italy and beyond by elucidating prognostic factors and developing quality-of-care indicators. Through rigorous data collection, analysis, and ethical oversight, the Tiresia project endorses the commitment of the research community to advancing evidence-based care and optimizing patient outcomes in sABI rehabilitation.
